### Study Interventions

#### Intervention Group: Nurse-Led, Acceptance and Commitment–Based, Supportive-Expressive Palliative Program

The intervention comprises 5 individual 60- to 90-minute sessions delivered over 3 months. The intervention is semistructured, with the intervener trained to facilitate discussions on 5 key themes adapted from CALM therapy and informed by findings from a previous cross-sectional study and qualitative interviews exploring the illness experience and care needs of individuals with PNDs in Hong Kong [31,32]. These themes include (1) symptom control and communication with health care professionals, (2) changes in sense of self amid progressive loss of function, (3) social support and relationships with family and friends, (4) spiritual support and finding meaning and life purpose in the context of illness, and (5) fears about disease progression and planning for the uncertain future and mortality. The time devoted to each theme and the sequence in which they are addressed will depend on the salience of the patients’ concerns during the sessions. The intervention aims to encourage patients to express concerns related to their diagnosis and treatment, describe their lived experiences and emotions, and identify current challenges. On the other hand, the intervention seeks to cultivate acceptance and promote value-driven behaviors, enhancing patients’ psychological flexibility in the face of illness, thereby enhancing psychospiritual well-being. The intervener will use acceptance and commitment–based techniques such as experiential exercises, mindfulness, and metaphors to facilitate the process. The intervention outline is shown in Table 1. The intervention will be delivered by registered nurses who have received standardized training in ACT and CALM therapy and will follow a structured intervention manual. Homework exercises will be provided to encourage participants to practice skills between sessions and maintain a record of their progress. A workbook with session content, along with audio instructions for mindfulness exercises and defusion and acceptance strategies, will be provided for home practice. In each session, participants will be encouraged to share their experiences and discuss any difficulties encountered during practice to consolidate learning and troubleshoot challenges.

**Table 1. T1:** An outline of the acceptance and commitment–based components with associated metaphors, experiential exercises, and home practice.

Session and main focus	Metaphors and/or experiential exercise	Home practice
Session 1		
Discuss the inevitability of emotional pain and how the mind can amplify psychological distress	Metaphors: “Mind is a ‘double-edged sword,’ / ‘problem-solving machine,’/ radio ‘doom and gloom’”	Coping strategies diary
Explore the emotional control agenda and consequences of trying to avoid unwanted thoughts and feelings	Coping strategies worksheet	—^a^
Introduce mindfulness as an alternative to cope with unwanted thoughts and feelings	Mindfulness exercise: “Acceptance techniques: Observe / breathe / expand / allow / expand awareness”	Diary of mindfulness practice: “Acceptance techniques”
Session 2		
Practice being present in the moment and experience thoughts and feelings in a nonjudgmental way	Mindful eating and body scan exercise	Diary of mindfulness practice: “Mindful body scan”
Discuss the consequences of struggling with or avoiding thoughts and feelings	Choice point diagram	—
Identify personal values and review whether behaviors align with these values	—	The Bull’s Eye values worksheet
Session 3		
Explore the problem of fusion with thoughts and feelings	Metaphor: “Hands as thoughts and feelings”	—
Practice defusion skills to step back and detach from difficult thoughts, feelings, or memories	Metaphor: “Emotional storm”; defusion exercise: “Dropping anchor”	Diary of defusion exercise: “Dropping anchor”
Notice how thoughts, feelings, and sensations get in the way of the things that are important in life	—	Physicalizing thoughts worksheet
Session 4		
Practice skills to notice the distinction between the self and thoughts, feelings, and sensations	Metaphor: “The sky and the weather”; defusion exercise: “The floating leaves on a moving stream”	Diary of defusion exercise: “The floating leaves on a moving stream”
Set value-driven, meaningful actions and realistic goals	Worksheet: “SMART goal setting”	Values and action card
Session 5		
Adopt an observer perspective on thoughts, feelings, and sensations	Metaphor: “The stage show”	—
Explore barriers to committed actions and strategies to overcome them	Worksheet: “What’s stopping you?”	—
Review mindfulness, defusion skills, metaphors, and exercises covered in previous sessions	—	—

a Not applicable.

The intervention aligns with recommended CALM therapy dosage (3 to 6 sessions over 3 to 6 months), with extended session length (60‐90 minutes) to incorporate ACT components. Evidence supports the feasibility and effectiveness of brief ACT-based interventions in palliative populations, with high adherence and promising effects on psychological distress [33]. Brief programs of no more than 5 sessions are associated with higher adherence, enhanced motivation, and better skill consolidation [24]. All sessions will be conducted in a private room at an academic institution or at the patients’ homes depending on their preference.

#### Control Group: Befriending Activity

Participants in the control group will receive 5 individual 30- to 60-minute befriending sessions over 3 months delivered by a trained registered nurse following the *Befriending Manual* [34]. Befriending serves as an active control condition designed to control for nonspecific therapeutic factors, including clinician contact time, attention and interpersonal support (eg, warmth and empathy), participant expectations of benefit, and the therapeutic alliance. Sessions focus on neutral, everyday topics of interest (eg, hobbies, pets, and current affairs) and avoid emotional exploration, problem-solving, or therapeutic techniques. The nurse will maintain a warm, friendly, and supportive stance throughout. For pragmatic reasons, extending unstructured befriending sessions beyond 60 minutes may lead to forced or unnatural conversations, which could inadvertently increase participant fatigue or lower retention rates.

### Outcome Evaluation

Outcomes will be assessed at baseline (T0), 1 week after the intervention (T1), and 3 months after the intervention (T2).

#### Primary Outcome

The Hospital Anxiety and Depression Scale (Chinese-Cantonese version) will be used to measure psychological distress. It is a 14-item self-report scale assessing anxiety and depression validated in neurological populations (Cronbach α=0.86) [27]. A higher score, rated on a 4-point Likert scale, indicates more severe stress [35]. Subscale scores ranging from 0 to 7 indicate “noncases,” scores from 8 to 10 suggest “possible cases,” and scores from 11 to 21 represent “probable cases” of anxiety or depression [36].

#### Secondary Outcomes

The Functional Assessment of Chronic Illness Therapy–Spiritual Well-Being 12-item scale (Chinese version) will be used to measure spiritual well-being. It assesses 3 constructs: belief, meaning, and sense of peace. All items are rated on a 5-point Likert scale (0=“not at all”; 4=“very much”). High scores indicate high levels of spiritual well-being (Cronbach α=0.711‐0.920 [37]).

The Meaning in Life Questionnaire (Chinese version) will be used to measure meaning in life [38]. It comprises 2 subscales: the presence of meaning in life and an individual’s drive and orientation toward finding meaning in life. It is rated on a 7-point Likert scale ranging from 1 (“absolutely untrue”) to 7 (“absolutely true”). Higher scores indicate higher degree of presence of meaning in life or search for meaning in life (Cronbach α=0.75‐0.85).

The Palliative Care Outcome Scale (Chinese version) will be used to assess symptom burden [39]. It comprises 10 items assessing physical symptoms, patient and family anxiety and well-being, information needs, and practical needs. It is scored on a 5-point Likert scale ranging from 0 (“not at all”) to 4 (“overwhelmingly”), with a total score of 40. It has shown good construct validity and test-retest reliability and acceptable internal consistency.

The Comprehensive Assessment of Acceptance and Commitment Therapy Processes (Chinese) will be used to measure psychological flexibility [40]. This 18-item scale consists of 3 subscales: openness to experience, behavioral awareness, and valued action. Each item is scored on a 5-point Likert scale from 1 (“strongly disagree”) to 5 (“strongly agree”). High scores indicate great psychological flexibility (Cronbach α=0.87).

The EQ-5D-5L (Chinese version) will be used to measure health-related QoL [41]. It includes 5 dimensions (mobility, self-care, usual activities, pain and discomfort, and anxiety and depression), each rated on 5 levels, and a visual analog scale (0‐100) measuring perceived overall health. Each dimension is scored on a 5-point response level ranging from “no problem” (level 1) to “extreme problem” (level 5). Health states are converted into a utility score (EQ-5D-5L index) using the Hong Kong value set [42], where 1 indicates full health and negative values indicate states worse than death.

The Brief Illness Perception Questionnaire (Chinese version) will be used to measure illness perception [43]. The 9-item scale evaluates cognitive and emotional representations of illness across domains such as consequences, timeline, control, identity, concerns, emotions, and coherence rated on scales from 0 to 10, with 1 open-ended causal item. Higher scores indicate more negative perceptions. However, higher scores on the personal control, treatment control, and coherence items reflect more positive perceptions and will be reverse scored when computing the total illness perception score. The instrument demonstrates acceptable reliability and validity and has been validated in palliative populations [43,44].

The Death and Dying Distress Scale (Chinese) will be used to assess distress about death and dying. This 15-item scale addresses fears about death and dying, the feeling of being a burden to others, and wasted opportunities [45]. It is rated on a 6-point Likert scale from 0 (“no distress”) to 5 (“very much distress”; Cronbach α=0.939).

### Baseline and Process Evaluation Measures

At baseline, sociodemographic and clinical data will be collected via self-report, including age, gender, marital status, educational level, religiosity, living status (eg, living alone, living with a spouse, living with family members, or other arrangements), financial assistance, disease onset, stage, comorbidities, and history of rehabilitation service use. Cognitive status will be screened using the Montreal Cognitive Assessment, Hong Kong version, a validated tool for Chinese patients with neurological conditions assessing executive function, attention, and verbal fluency [46]. Intervention expectancy and satisfaction will be measured using an adapted credibility and expectancy questionnaire [47]. Participants will rate the intervention’s logicality, usefulness, helpfulness, and perceived and expected improvement, as well as confidence in recommending it to others. The original English version of the credibility and expectancy questionnaire demonstrates satisfactory internal consistency (Cronbach α=0.79-0.90).

Following quantitative data collection, a subsample of participants will undergo individual semistructured interviews to explore perceived effects and acceptability of the intervention. Interviews will be conducted at home or in academic settings, audio recorded, and guided by open-ended questions.

### Data Collection Procedure

Potential participants will be provided with a general overview of the study. A research assistant will set an appointment with those patients who meet the inclusion criteria and agree to participate in the study. In the face-to-face interview, a research nurse will check the eligibility criteria and perform the baseline evaluation (T0). Information on all screened patients and reasons for exclusion will be recorded. Participants will receive a cash reward of HKD 100 (approximately US $13) per each assessment (T0, T1, and T2). To control for participant expectancy, both groups will be introduced with identical positive phrasing regarding the potential benefits of the interventions. After baseline assessment, participants will be randomly assigned to the 2 groups on a 1:1 basis using the method of permuted block with random block sizes of 4, 6, and 8 by an independent researcher not involved in the assessments. The allocation list will be computer generated by an independent researcher and concealed from other researchers and participants until the time of assignment. An independent research assistant blinded to the group allocation will collect the postintervention questionnaires. Figure 1 shows the flowchart of the study implementation plan.

**Figure 1. F1:**
[figure not shown]
CONSORT (Consolidated Standards of Reporting Trials) flow diagram indicating the study schedule of enrollment, interventions, and assessments.

### Data Analysis

Quantitative data will be analyzed using SPSS (version 28.0.1; IBM Corp) following the intention-to-treat principle. Descriptive statistics will summarize baseline characteristics, and group comparability will be examined using chi-square or Fisher exact tests. Linear mixed-effects models will assess intervention effects on primary and secondary outcomes, with time, group, and group-by-time interaction included as fixed effects. Between-group differences will be estimated using linear contrasts. Model assumptions will be checked using normal probability plots. Missing data will not be imputed as mixed-effects models accommodate incomplete observations [48]. A 2-sided significance level of 5% will be adopted. To account for the variations in therapist contact and attention, we will log the exact duration (in minutes) of each session for every participant. In sensitivity analysis, total contact time will be included as a covariate in the linear mixed-effects models to statistically control for the potential confounding effect of extra nurse contact.

Qualitative interviews will be transcribed verbatim and managed using NVivo (version 12; Lumivero). Two researchers will independently conduct inductive thematic analysis following a 5-step approach [49]. Codes will be organized into categories and themes to identify recurring patterns. An audit trail will enhance rigor, and discrepancies will be resolved through discussion. Qualitative findings will complement and enrich interpretation of the quantitative results.

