## Methods

### Study Design, Setting, and Sampling

This sequential mixed methods study comprises a 2-arm randomized controlled trial followed by a qualitative study. This protocol adheres to the SPIRIT (Standard Protocol Items: Recommendations for Interventional Trials) checklist [26]. Adults with PNDs will be recruited from outpatient neurology clinics (Queen Mary Hospital and Tung Wah Hospital) and patient support groups (Hong Kong Parkinson’s Disease Foundation and Hong Kong Neuro-Muscular Disease Association) in Hong Kong.

Eligible participants are adults (≥18 years) diagnosed with PNDs (eg, PD, MS, motor neuron disease, multiple system atrophy, progressive supranuclear palsy, muscular dystrophy, spinocerebellar ataxia, or spinal muscular atrophy) with psychological distress indicated by a Hospital Anxiety and Depression Scale score of 8 or higher on either the depression or anxiety subscale (sensitivity and specificity of 0.75‐0.89) [27] and able to communicate in Cantonese.

Exclusion criteria are severe cognitive impairment (Abbreviated Mental Test <6) [28], recent psychotherapy (within 6 months), or severe psychiatric or medical comorbidities limiting participation.

Power analysis using G*Power was performed to estimate the required sample size. Previous studies of mindfulness- and acceptance-based interventions have reported large effect sizes (0.96‐1.14) in people with MS [29] and moderate to large effects for anxiety (*d*=0.58) and depression (*d*=0.74) in PD [30]. Given the use of an active control (befriending), a conservative moderate effect size of 0.58 was assumed for the primary outcome (anxiety and depressive symptoms). Using a Bonferroni-adjusted significance level of 2.5% and 80% power, 118 participants (59 per arm) are required. Allowing for 15% attrition, the final target sample size is 138 participants (69 per arm).

For the subsequent qualitative phase, approximately 30 participants from the intervention group will be invited for postprogram semistructured interviews, with the final sample size guided by data saturation. Purposive maximum variation sampling (eg, gender, age, and educational level) will be used to capture diverse experiences. Additional participants will be recruited until no new themes emerge.

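### The planned mixed model leaves each arm its own baseline mean and names no baseline adjustment, so its contrasts are unbiased but less precise than the collected data allow

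*Protocol article*

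**What the plan says.** The Data Analysis section lists the fixed effects of the linear mixed models for primary and secondary outcomes: "with time, group, and group-by-time interaction included as fixed effects. Between-group differences will be estimated using linear contrasts". It names no baseline covariate and no constraint of equal baseline means. It does not say whether the contrast is the group difference at a follow-up visit or the difference in change from T0.

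The Outcome Evaluation section sets three assessments: "Outcomes will be assessed at baseline (T0), 1 week after the intervention (T1), and 3 months after the intervention (T2". According to Data Collection Procedure, randomisation follows the baseline assessment, and "participants will be randomly assigned to the 2 groups on a 1:1 basis".

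The sample size in Study Design, Setting, and Sampling rests on this assumption: "a conservative moderate effect size of 0.58 was assumed for the primary outcome (anxiety and depressive symptoms". The result is: "Using a Bonferroni-adjusted significance level of 2.5% and 80% power, 118 participants (59 per arm) are required". The section does not say whether 0.58 is standardised by the SD of the raw score or of the change score, and it gives no correlation between baseline and follow-up.

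**The concern.** T0 precedes randomisation, so any difference between the arms at baseline is due to chance. A model with group, time and group-by-time effects that includes T0 as an outcome does not use this fact. It estimates a separate baseline mean in each arm.

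Two contrasts can be taken from such a model. With complete data, the difference in change subtracts the whole chance baseline difference, which is too much whenever the correlation is below 1 and variances are equal. The difference at T1 or T2 subtracts none of it, which is too little whenever the correlation is above 0. The efficient analysis subtracts the fraction that the correlation justifies.

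The entry rule leaves real baseline spread on each subscale to use. Participants qualify "with psychological distress indicated by a Hospital Anxiety and Depression Scale score of 8 or higher on either the depression or anxiety subscale", so someone eligible on anxiety may score low on depression, and the reverse.

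What is at stake is the width of the confidence intervals for the primary and secondary outcomes, in a trial that had enrolled 132 of its 138 participants by January 2026. There is little room left to gain precision by recruiting.

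**Working it through.** **Inputs from the protocol.** d = 0.58, alpha 2.5%, 59 evaluable per arm, 1:1 allocation. Two-sided testing comes from the Data Analysis section ("A 2-sided significance level of 5% will be adopted"). That section's 5% differs from the 2.5% used for sizing, which is a separate matter; 2.5% is used here.

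**Assumption.** The correlation rho between T0 and a follow-up visit is not in the document. The range 0.3 to 0.7 is assumed. Variances at T0 and follow-up are first taken as equal.

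**Step 1: reproduce the plan's figure.** A two-sample t-test (noncentral t, two-sided 0.025, d = 0.58) needs 58 per arm for 80% power (80.2%). At the stated 59 per arm, the noncentrality is 0.58 × sqrt(59/2) = 3.15, the critical value is 2.27 and power is 80.9%. The 118 therefore agrees to within two participants with a plain two-group comparison that takes no credit for baseline. For attrition, 118/0.85 = 138.8, against the stated 138.

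**Step 2: variance of each analysis**, in units of the follow-up variance, complete data:
- group difference at T1 or T2: 1
- difference in change, baseline means free: 2(1 − rho)
- baseline-adjusted or common baseline mean: 1 − rho²

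The ratios to the adjusted analysis are 2(1 − rho)/(1 − rho²) = 2/(1 + rho) for the change contrast and 1/(1 − rho²) for the follow-up contrast.

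| rho | change / adjusted | follow-up / adjusted |
|---|---|---|
| 0.3 | 1.40/0.91 = 1.54 | 1/0.91 = 1.10 |
| 0.5 | 1.00/0.75 = 1.33 | 1/0.75 = 1.33 |
| 0.7 | 0.60/0.51 = 1.18 | 1/0.51 = 1.96 |

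For every rho strictly between 0 and 1, both ratios exceed 1.

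**Step 3: power if d = 0.58 is on the raw-score SD.** The noncentrality is 3.15/sqrt(variance), with 59 per arm and two-sided 0.025.

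| rho | change | follow-up | adjusted |
|---|---|---|---|
| 0.3 | 65.3% | 80.9% | 84.7% |
| 0.4 | 72.7% | 80.9% | 87.7% |
| 0.5 | 80.9% | 80.9% | 91.3% |
| 0.6 | 89.3% | 80.9% | 95.1% |
| 0.7 | 96.3% | 80.9% | 98.3% |

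Power of 80% is reached once the variance is about 1.02 or less. Setting 2(1 − rho) = 1.02 gives rho = 0.49.

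**Step 4: power if d = 0.58 is on the change-score SD.** The change contrast has 80.9% power at any rho. The adjusted analysis has 94.8%, 91.3% and 87.3% at rho 0.3, 0.5 and 0.7.

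**Step 5: unequal variances.** Let k be baseline SD divided by follow-up SD. The change variance is then 1 + k² − 2·rho·k. With k = 0.8 (illustrative, not in the document) this is 1.64 − 1.6·rho:
- rho 0.3: 1.16, ratio 1.16/0.91 = 1.27, power 74%
- rho 0.5: 0.84, ratio 0.84/0.75 = 1.12, power 88%

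The change contrast then falls below 80% only for rho below (1.64 − 1.02)/1.6 = 0.39.

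**Step 6: check with dropout.** Generalised least squares for the three-visit model, with 69 per arm at T0, 59 at T1 and T2, compound symmetry and a normal approximation, gives at rho 0.3: change 68.8%, follow-up 82.4%, common baseline mean 85.6%. At rho 0.5 the figures are 83.3%, 83.3% and 91.9%. The ordering is unchanged at 0.3, and the change and follow-up contrasts tie at 0.5 as in Step 3.

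**The case against.** The strongest reply is that nothing here is an error. A free-baseline group-by-time model is standard, its contrasts are unbiased under randomisation, and the sample size takes no credit for baseline correlation, so adjustment would only add power beyond the target. This stands, and it is why the point concerns efficiency only.

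A second reply is that a statistical analysis plan, not shown, may settle the contrast, the covariance structure and the visits used as outcomes. That is fair for those details. The fixed effects, however, are listed in the article, the list reads as complete, and T0 as one of the times is its natural reading.

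Third, the equal-variance figures for the change contrast may overstate the loss. An entry threshold on HADS can shrink the baseline SD as well as the correlation. With k = 0.8, the ratio at rho 0.3 drops from 1.54 to 1.27. This stands as a limit on the size.

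A reader might go further and infer three things that the document does not support:
- **The trial is underpowered.** The article's hypotheses speak of greater improvement, which points towards a change contrast, and the entry rule makes a lower correlation plausible. But the article fixes neither the contrast, nor the SD behind d, nor the correlation.
- **Regression to the mean biases the comparison.** Both arms pass the same entry rule before randomisation, so the expected regression is the same in each and cancels. Only chance imbalance remains, and the standard error already reflects it.
- **A constrained model gains by keeping participants with only T0.** The planned model keeps them too when T0 is an outcome.

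**Conclusion.** The model as stated is valid but less efficient than it need be, whichever contrast is meant. Under equal variances and an assumed correlation of 0.3 to 0.7, its variance exceeds that of the baseline-adjusted analysis by 18% to 54% for the difference in change and by 10% to 96% for the difference at T1 or T2. The change-contrast loss is smaller if the baseline SD is below the follow-up SD.

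The stated 118 and 80% are not shown to be wrong. A shortfall needs three things together: the contrast is the difference in change, d = 0.58 refers to the raw-score SD, and the correlation is below about 0.49 (lower still if the baseline SD is the smaller). If the contrast is the group difference at T1 or T2, power is 80.9% at any correlation.

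**What to change.** Before analysis starts, replace the fixed-effects sentence with a constrained longitudinal model: T0, T1 and T2 as outcomes; time, group-by-T1 and group-by-T2 as fixed effects; no group effect at T0, so that the arms share one baseline mean; unstructured covariance. Report the T1 and T2 between-group differences from it, for primary and secondary outcomes. This also names the contrast, which the article leaves open.

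A close alternative is to model T1 and T2 as outcomes with the baseline score of the same scale as a covariate.

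The cost is one line of model specification, which SPSS can fit with two indicator variables. No new data are needed. The article states that no outcome analyses have been done, so the change can still be made without knowledge of results.

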**Methods:**

This is a 2-arm, parallel-group randomized controlled trial using an explanatory sequential mixed methods design. A total of 138 participants with PNDs will be recruited and randomized 1:1 to either the intervention group (n=69) or a befriending control group (n=69). The intervention consists of five 60- to 90-minute individual sessions delivered over 3 months by trained nurses integrating acceptance and commitment therapy–based strategies (eg, mindfulness, cognitive defusion, and value-guided action) with supportive-expressive approaches. The control group receives five 30- to 60-minute active befriending sessions. The primary outcome is psychological distress, assessed via the Hospital Anxiety and Depression Scale. Secondary outcomes include spiritual well-being, meaning in life, psychological flexibility, illness perception, palliative care needs, health-related quality of life, and death anxiety. Assessments will be conducted at baseline (T0), 1 week after the intervention (T1), and 3 months after the intervention (T2). Quantitative data will be analyzed using linear mixed-effects models under the intention-to-treat principle. Following the intervention, a purposive subsample will undergo semistructured qualitative interviews to explore intervention acceptability and participant experiences.

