### Aims and Hypotheses

This study aims to (1) examine the effects of a nurse-led, acceptance and commitment–based, supportive-expressive palliative care program on anxiety and depressive symptoms (primary outcomes) and spiritual well-being, meaning in life, palliative care needs, psychological flexibility, illness perception, health-related QoL, and death anxiety (secondary outcomes) among individuals with PNDs compared to a befriending control group; and (2) explore participants’ perceptions and experience of the palliative program, specifically identifying its perceived utility, mechanisms of change (how and why it works or fails to work), and contextual factors influencing intervention acceptability, motivation, and real-life practice.

It is hypothesized that individuals with PNDs who receive the palliative program will demonstrate significantly greater improvement in psychological distress at the postintervention follow-up (T1) and 3 months after the intervention (T2) compared with those receiving the befriending control. In addition, it is hypothesized that participants in the palliative program will show greater positive changes in secondary psychological, spiritual, and palliative outcomes relative to the control across the same time points.

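### The trial is sized at a Bonferroni-adjusted 2.5% level but the analysis section adopts 5% without adjustment, and the number of primary tests is not settled

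*Protocol article*

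**What the plan says.** All references are to the protocol article.

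- **Study Design, Setting, and Sampling:** "Using a Bonferroni-adjusted significance level of 2.5% and 80% power, 118 participants (59 per arm) are required". The assumed standardised effect is 0.58, described as being for the primary outcome (singular), with anxiety and depressive symptoms in brackets. The target is then raised for attrition: "Allowing for 15% attrition, the final target sample size is 138 participants (69 per arm)".
- **Data Analysis:** after describing mixed models for the primary and secondary outcomes, the section states: "A 2-sided significance level of 5% will be adopted". It mentions no adjustment and no separate level for the primary outcome. No other section carries 2.5% into the analysis.
- **Aims and Hypotheses:** the plural is used, "anxiety and depressive symptoms (primary outcomes)". The main hypothesis covers two time points: "significantly greater improvement in psychological distress at the postintervention follow-up (T1) and 3 months after the intervention (T2)".
- **Abstract, Methods:** one outcome is named, "The primary outcome is psychological distress, assessed via the Hospital Anxiety and Depression Scale". The Primary Outcome section is also worded for one construct, although it gives caseness bands for the subscales.

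**The concern.** The significance level that fixed the sample size is not the level stated for the analysis. A subscale p-value between 0.025 and 0.05 would be a positive primary result under Data Analysis and a negative one under the level used for sizing.

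The number of primary tests is also open. A Bonferroni level of 2.5% implies two tests, but the article does not say which two. Anxiety and depression is the natural reading, yet T1 and T2 both appear in the main hypothesis, and other sections describe a single outcome, which would need no split.

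At stake are the rule for declaring the trial positive and its type I error. If this is left open until results are known, the choice of threshold, subscale and time point could follow the data.

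**Working it through.** **Inputs from the article.** Standardised effect d = 0.58, power 80%, 1:1 allocation, 15% attrition, level 2.5% (sizing) and two-sided 5% (analysis). **Assumed here:** correlations between test statistics, since the article gives none.

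**1. Reproducing the stated sample size.** Two-sample comparison of means, n per arm.

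Normal approximation: n = 2(z₁₋α/₂ + z₀.₈₀)² / d².

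- α = 0.025: 2(2.241 + 0.842)² / 0.58² = 56.5, so 57 per arm.
- α = 0.05: 2(1.960 + 0.842)² / 0.58² = 46.7, so 47 per arm.

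Noncentral t, with 2n − 2 degrees of freedom and noncentrality d√(n/2):

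| Two-sided level | Smallest n per arm for 80% | Total | Power at 59 per arm |
|---|---|---|---|
| 2.5% | 58 | 116 | 80.9% |
| 5% | 48 | 96 | 87.8% |

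The stated 118 is within 2 of the 2.5% result and 22 above the 5% result, so the trial was sized for a two-sided 2.5% test. Attrition: 118 / 0.85 = 138.8, against a stated 138; the difference is trivial.

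**2. Familywise error with two primary tests, success on either.** Independent tests: 1 − (1 − α)². Correlated tests: bivariate normal.

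| Correlation | Each at 5% | Each at 2.5% |
|---|---|---|
| 0 | 9.75% | 4.94% |
| 0.5 | 9.1% | 4.7% |
| 0.7 | 8.3% | 4.3% |
| 0.8 | 7.8% | 4.0% |

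**3. Familywise error if T1 and T2 both count (four tests).** Independent: 1 − (1 − α)⁴. Correlated: simulated multivariate normal, with an assumed 0.6 between subscales and 0.6 between times.

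| Level per test | Independent | Correlation 0.6 |
|---|---|---|
| 5% | 18.5% | about 15% |
| 2.5% | 9.6% | about 8% |

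Testing each subscale at 2.5% therefore controls the error at 5% only if one time point is primary. An equal split over four tests is 5% / 4 = 1.25% each; power at 59 per arm is then 72.9%, and 80% would need 68 per arm with data.

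**The case against.** The two levels can be reconciled. A Bonferroni-adjusted 2.5% is 5% divided by two, so it presupposes an overall 5%. The sentence in Data Analysis may state that overall level, with the sample-size paragraph giving the level per outcome. On that reading there is no inflation. A condensed article may also leave the detailed multiplicity rule to an analysis plan that is not shown. And sample size is not at risk: 59 per arm gives at least 80% power for a test at either level.

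Much of this stands. A reader might infer that the planned analysis has an 8–10% familywise error as a matter of fact. The article does not support that: it needs two primary tests, each at 5%, success on either, and a correlation of no more than about 0.75. The article gives no success rule and no correlation, and with a single HADS score at one time point there is no inflation at all. Nor does the article show that the trial is underpowered.

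What does not stand is that nothing needs correcting. The point is not a missing detail. The article prints two levels without linking them, and words the primary outcome in two ways. An analyst following Data Analysis literally would use 5% for every outcome. If instead there is one primary outcome at one time point, the Bonferroni statement and the plural are wrong.

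**Conclusion.** The inconsistency is real and bears on the primary claim. The sample size fits a two-sided 2.5% test, while the analysis section states 5% with no adjustment, and the article does not settle whether there are one, two or four primary tests.

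The effect on type I error is conditional. Two subscales each at 5% with success on either give 9.75% (independent) to 7.8% (assumed correlation 0.8). Four tests at 5% give 18.5% if independent and about 15% at assumed correlations of 0.6. There is no inflation if 5% is the overall level split over the primary tests, or if one score at one time point is primary. The wording needs correcting on every one of these readings.

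**What to change.** Settle this before any outcome analysis. The Results section reports 132 enrolled as of January 2026 and no outcome analyses to date, so it can still be done prospectively.

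**If the two subscales are primary.** In Data Analysis, replace the single-level sentence with text such as: *The overall two-sided significance level for the primary outcomes is 5%, split as 2.5% for HADS-Anxiety and 2.5% for HADS-Depression, each tested at [T1 or T2, to be named]. The other time point is secondary* (or: *is tested only after success at the first*). If both time points are to be primary, split the 5% across all four tests and restate the power.

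**If a single HADS total at one time point is primary.** Keep 5%, delete the Bonferroni statement, name the time point, and restate the power as 88% at 59 per arm under d = 0.58.

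In either case, align the wording of the primary outcome in the Abstract, Aims and Hypotheses, the sample-size paragraph and the Primary Outcome section.

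**Cost.** Wording only. With two subscales at one time point, the stricter threshold gives about 81% rather than 88% power per outcome at 59 per arm, which is what the trial was sized for, and the target of 138 does not change. An equal four-way split would lower power to about 73% per test.
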